#### 2.5.3. Rescue and Concomitant Treatment

Participants in both groups will be consistent in usage, dosage, and trial period. The painkiller (acetaminophen) will be allowed to relieve symptoms, if unbearable pain remains after taking the study drugs for two hours. During the treatment period, use of CM decoction, other CM products, acupuncture, massage, or cupping therapy with the CM function of moving *qi* and/or activating *blood* will be forbidden.

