Chinese herbal medicine (CHM) has a long history in China and other regions of Asia. It is the main form of CM and could provide further options for headache treatment. The Chinese herbal formula Xuefu Zhuyu (XFZY) is the representative, classical CHM prescription for the treatment of headache. It has been widely used in the treatment of headache with *Qi-stagnation and Blood-stasis* pattern (QBS) (also called Zheng in CM). XFZY oral liquid is a patented product, which has been approved by the China Food and Drug Administration in 2002 (Ref No. Z10950063) [20]. It is an improved dosage form of XFZY decoction [21], which strictly follows the original prescription and dosage of XFZY decoction. Hence, they have the same function in promoting and activating the flow of *qi* and *blood* to treat QBS. This treatment has been utilized since the Qing Dynasty. XFZY consists of Bupleuri Radix (chaihu), Angelicae Sinensis Radix (danggui), Rehmanniae Radix (shengdihuang), Paeoniae Radix Rubra (chishao), Carthami Flos (honghua), Persicae Semen (taoren), Aurantii Fruxtus (zhiqiao), Glycyrrhizae Radix et Rhizoma (gancao), Chuangxiong Rhizoma (chuanxiong), Achyranthis Bidentatae Radix (niuxi), and Platycodonis Radix (jiegeng). A document to describe the components of the XFZY and pharmaceutical production processes were offered in supplementary file S1. Experimental studies have revealed that XFZY has an anticoagulating effect and improves microcirculation by reducing blood viscosity [22–25]. Clinical studies have shown that XFZY is effective in treating headache disorders, especially in migraine [26, 27], but the evidence of XFZY for TTH is absent. Therefore, the aim of this trial is to investigate whether the efficacy and safety of XFZY for TTH patients with QBS is superior to placebo.

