### 2.5. Interventions

#### 2.5.1. Experimental Group

In the experimental group, participants will take 20 ml XFZY orally, 3 times a day, for 4 weeks. After treatment, an 8-week follow-up will be conducted. XFZY oral liquid will be manufactured in strict accordance with the standards of the Chinese Pharmacopoeia (2015) [30], and the process strictly abides by the Good Manufacturing Practice (GMP). XFZY will be manufactured by Jilin Aodong Pharmaceutical Group Co., Ltd., in line with the requirements of GMP.

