### 2.7. Outcome Measures

#### 2.7.1. Primary Outcome

The primary outcome is the change in mean headache intensity from the baseline to the end of the 12th week. Headache intensity will be measured along a 10 cm visual analogue scale (VAS), with “none” and “very severe” at the extremes of the spectrum.

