#### 2.7.2. Secondary Outcomes

The secondary outcomes are the area-under-the-headache curve (AUC), calculated by the sum of the daily headache duration (hours) multiplied by the daily headache intensity for each observed period and, then, divided by the observation period; headache frequency, defined as a ≥50% reduction by number of days with a headache or attacks per evaluation period; headache hours in each observed period; rescue medication use for unbearable pain 2 hours after taking the drugs; QBS pattern measurement by a qualified CM physician; quality of life measured by the EuroQol-5-Dimensions-5-Level (EQ-5D-5L) granted by the EuroQol Group [32, 33]; global evaluation of medication assessed by a simple verbal scale; health economic indexes calculated by the cost of registration, laboratory testing, drugs (other than the experimental drug), hospital admission, transportation, average monthly income, and costs incurred by family caregivers. Participants will be asked to complete a headache diary throughout the trial. The primary outcome and the first four secondary outcomes will be extracted from the headache diary.  Table 2 shows the timing for all outcome measures in the study.

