### 2.10. Statistical Analysis

The statistical analysis will be performed on the basis of a pre-established statistical analysis plan. Data analysis will be based on the intent-to-treat (ITT) and per protocol (PP) principles and will be conducted by independent qualified statisticians blinded to treatment allocation. Two-tailed *p* values less than 0.05 will be considered statistically significant. Missing data will be replaced by the multiple imputation method. All analyses will be conducted with SPSS version 18.0 (IBM SPSS Inc, Armonk, New York, USA) or SAS 9.2 (SAS Institute Inc., Cary, USA). Continuous variables will be expressed as mean ± SD if data are normally distributed. Data not normally distributed will be presented using the median and interquartile range (IQR). Categorical variables will be expressed as counts and percentages.

For primary and secondary outcomes, a full analysis set including participants with at least one treatment and outcome assessment and a perprotocol analysis set containing 4-week treatment,will be employed to compare the changes between groups with an independent *t*-test, respectively; repeated measures of analysis of variance or a liner mixed model will be applied to analyze the changes measured at different time points. Sex, age, course of disease, and center, as well as other covariates will be considered in the statistical model.

For safety assessments, a safety analysis set with all subjects who took the drug at least once will be adopted to detect whether the AE proportions are significant between the two groups. This will be performed with either a *χ*^2^ test or Fisher's exact test. All AEs will be coded based on the Chinese version of the Medical Dictionary for Regulatory Activities (MedDRA).

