## 3. Discussion

To our knowledge, this is the first study to investigate the efficacy and safety of XFZY for TTH, compared to a placebo treatment. Although existing pharmacological and nonpharmacological treatments have been shown to be helpful [11, 41–43], the evidence available for treatment efficacy is limited to small magnitude or adverse events. Hence, new pharmacologic treatments are expected.

Both ETTH and CTTH patients are target populations of this study. However, they are categorized differently according to ICHD-3 criteria and have variant pathogenesis [44, 45]. Yet, the two diseases can be identified by the same CM pattern and are judged by similar signs and symptoms. QBS is a common TTH pattern. XFZY is a classical formula that promotes the flow of *qi* and *blood* in CM. Hence, we will conduct a randomized, double-blinded, placebo-controlled trial to evaluate the effect of XFZY for TTH with QBS.

Patient-centered outcomes are the focus of this study. This is in contrast to previous studies which have concentrated on rapid relief and being pain-free after 2 h, as recommended by HIS [31]. VAS and EQ-5D-5L are reported by the subjects, and the former is the primary outcome for evaluating headache intensity, while the latter measures the quality of life. The long-term effect deserves more attention than the frequent occurrence of headache. Therefore, our study period includes 4 weeks of treatment and 8 weeks of follow-up, in order to observe the long-term response.

TTH has immense public health costs, both in China and around the world, owing to its high prevalence among the general population, especially with regard to indirect costs (i.e., lost work and leisure time). As such, the economic costs are increasing. Data from a cross-sectional survey has shown mean annual costs of €303 per capita for tension-type headache in Europe [46]. Among them, the direct cost is €25, less than CNY 468 per person in China [47]. In order to assess costs and cost-effectiveness for patients taking XFZY compared with patients receiving placebo, we will calculate the health economic index as one of the outcome measures.

In conclusion, the results of this study are expected to provide evidence of high methodological quality on the efficacy and safety of XFZY for TTH.

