## Figures and Tables

**Figure 1 fig1:**
[figure not shown]
Study flow chart.

**Table 1 tab1:** QBS diagnosis scale.

Symptoms/signs	Yes	No	Score
Pain	9	0	
Irritability/depression	16	0	
Distending pain	2	0	
Scurry pain	6	0	
Chest distress	0.5	0	
Lumps in body	7	0	
Petechia in the tongue	4	0	
Purplish tongue	1	0	
Unsmooth pulse	4	0	
Deep pulse	2	0	
Total score If ≥20 points, diagnosed as QBS			

Notes: pain includes stomachache, abdominal pain, low back pain, dysmenorrhea, breast pain, and limb pain. QBS: *Qi*-stagnation and Blood-stasis pattern.

**Table 2 tab2:** Outcome measures.

Domain	Measure	Time (weeks)
*Primary*		
Mean pain intensity of headache change	10 cm VAS with “none” and “very severe” at either end	0, 1, 2, 4, 8, 12
Secondary		
AUC	Calculated by the sum of the daily headache duration (hours) multiplied by the daily headache intensity in each observed period and, then, divided by the observation period	0, 1, 2, 4, 8, 12
Headache frequency	Defined as a ≥50% reduction by the number of days with a headache or attacks per evaluation period; headache hours for each observed period	0, 1, 2, 4, 8, 12
Headache hours	The total hours in each observed period	0, 1, 2, 4, 8, 12
Rescue medication use	Records the number of participants using the rescue medication and the total dosage per week	0, 1, 2, 4, 8, 12
QBS measurement	Evaluated by a qualified CM physician	0, 1, 2, 4, 8, 12
Quality of life	EQ-5D-5L	0, 4, 12
Global evaluation of medication	A simple verbal scale: very poor, poor, neutral, good, very good	4
Health economic indexes	Registration costs, laboratory tests, drugs (other than the experimental drug), hospital admission, transportation, average monthly income, costs incurred by family caregivers	0, 1, 2, 4

VAS: visual analogue scale, AUC: area-under-the-headache curve. EQ-5D-5L: EuroQol-5-Dimensions-5-Level.

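### Low-cost improvement: the ban on qi-moving or blood-activating CM therapies stops at week 4, eight weeks before the primary outcome is read, so either arm may take marketed XFZY before the week-8 and week-12 readings

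*Protocol article*

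**What the plan says.** All references are to the protocol article.

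- **Ban (2.5.3).** "During the treatment period, use of CM decoction, other CM products, acupuncture, massage, or cupping therapy with the CM function of moving". The sentence goes on to name qi and blood as the targets of these therapies, and it forbids them for that period. Acetaminophen is the named rescue drug.
- **Treatment and follow-up (2.5.1, 2.5.2).** Study drug is taken for 4 weeks in both arms. "After treatment, an 8-week follow-up will be conducted" in the experimental group, and 2.5.2 gives placebo the same follow-up. The Discussion treats the two periods as distinct and gives the purpose of the second: "our study period includes 4 weeks of treatment and 8 weeks of follow-up, in order to observe the long-term response".
- **Primary outcome (2.7.1).** "The primary outcome is the change in mean headache intensity from the baseline to the end of the 12th week". Table 2 schedules VAS readings at weeks 0, 1, 2, 4, 8 and 12.
- **Availability of the test product (Introduction).** "XFZY oral liquid is a patented product, which has been approved by the China Food and Drug Administration in 2002". The same section describes XFZY as in wide use for headache with the pattern that 2.2 requires for entry.
- **Diary (2.7.2).** "Participants will be asked to complete a headache diary throughout the trial".

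**The concern.** The restriction and the endpoint cover different periods. The ban ends when study drug ends, and for the next 8 weeks nothing stated in the article stops a participant from taking the test product itself or a close relative of it. The opportunity is real: these are patients with recurrent headache and the matching CM pattern, whose study drug has just stopped, and the product is approved for sale.

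What is at stake is the meaning and size of the week-12 estimate. The Discussion says that follow-up is there to show the long-term response. Two mechanisms could distort that:

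- Placebo participants who take XFZY after week 4 move toward the XFZY arm and shrink the difference.
- XFZY participants who carry on with it are no longer showing the lasting effect of a 4-week course.

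Randomisation and blinding do not prevent either. Use after week 4 can depend on how a participant fared up to week 4, and so can differ by arm.

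**Working it through.** **1. Timing.** The ban covers weeks 1 to 4 and the outcome runs to week 12. The gap is 12 − 4 = 8 weeks. Table 2 has five post-baseline VAS readings (weeks 1, 2, 4, 8, 12). Two of them (weeks 8 and 12), including the time point named in 2.7.1, fall after the ban ends.

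**2. The plan's own effect.** Section 2.9 assumes mean changes of 4.46 (XFZY) and 2.14 (placebo), each with SD 1.5. The planned difference is 4.46 − 2.14 = 2.32 cm. The plan gives no figure for use of these products in weeks 5 to 12, so there is none to reproduce. What follows rests on assumed values.

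**3. Dilution from the placebo arm.** Let c be the share of placebo participants who use XFZY in weeks 5 to 12, and e the gain per user in cm at week 12. Assume no added gain in the XFZY arm. Then:

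fall in the week-12 difference = c × e

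With e at its planned maximum of 2.32 cm:

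| c | Fall (cm) | Remaining difference (cm) |
|---|---|---|
| 5% | 0.05 × 2.32 = 0.12 | 2.20 |
| 10% | 0.10 × 2.32 = 0.23 | 2.09 |
| 20% | 0.20 × 2.32 = 0.46 | 1.86 |

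With a smaller assumed gain of e = 0.5 cm, 10% use costs 0.10 × 0.5 = 0.05 cm. At 10% use the range is therefore 0.05 to 0.23 cm.

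**4. Effect on the test against zero.** After 15% loss, 87 × 0.85 = 73.95, so take 73 per arm. The standard error is 1.5 × √(2/73) = 0.248. At c = 10% with full gain, 2.088 / 0.248 = 8.4 standard errors; at c = 20%, 1.856 / 0.248 = 7.5. Both are far beyond 1.96, and two-sided 5% power stays above 99%.

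**5. Continued use in the XFZY arm.** No figure can be put on this. The 2.32 cm is already credited to that arm, and the documents say nothing about what further XFZY would add after week 4. The direction is toward apparent durability; the size is unknown.

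**The case against.** The best defence is that restricting co-treatment during dosing and allowing ordinary care afterwards is a recognised design. The week-12 comparison of randomised arms is then a valid estimate of a 4-week course followed by usual care, and the Discussion does not say that the long-term response must be free of other therapy. This stands as far as it goes: the plan contains no contradiction. But the article does not say that this is the intended meaning, and usual care that includes the test product itself is a poor basis for judging how long a 4-week course lasts.

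A second defence is that a journal article condenses the full protocol. That does not remove the point, because the time limit on the ban is stated expressly. It does rule out several stronger readings that a reader might infer:

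- **That the per-protocol analysis would keep such users.** Section 2.10 describes "a perprotocol analysis set containing 4-week treatment", a short phrase. Detailed exclusions are commonly left to the statistical analysis plan, so the inference is unsafe.
- **That use would go unrecorded.** Table 2 collects the costs of other drugs only to week 4, but a concomitant-medication log may exist in the full protocol.
- **That equal use in both arms cancels out, or that continued use could add up to 2.32 cm per user in the XFZY arm.** Neither follows. Adding 2.32 to 4.46 gives a mean change of 6.78 cm on a 10 cm scale, in patients eligible from 3 cm. With 10% use in both arms, and full gain only in the placebo arm, the difference still falls by 0.23 cm.
- **That the trial loses power against the 1.7 margin in 2.9.** The t-test in 2.10 does not mention that margin, so power against it is no basis for this point.

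The last objection is burden. A longer ban triples the restricted period, from 4 to 12 weeks, after study drug has stopped. That is a real cost, taken up with the remedy.

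**Conclusion.** The point holds as a modest design improvement, not as an error. The ban is set too short for its own endpoint: for the 8 weeks before the primary reading, the stated rule permits open-label use of the test product in both arms. Neither the net direction nor the size of the effect can be derived from the documents. The 0.23 cm figure is an illustration that assumes 10% use in the placebo arm, the full planned gain in those users and no added gain in the XFZY arm. A conclusion of superiority to zero would not be at risk under these figures. What would suffer is the estimate of effect at week 12 and its reading as the lasting benefit of a 4-week course. The documents do not show that participants will use these products, only that nothing stated forbids it.

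**What to change.** 1. In 2.5.3, replace the opening time limit with a period running from baseline to the end of week 12, and name marketed XFZY in any dosage form among the restricted products.
2. Record any such use in weeks 5 to 12 (product, dose, dates) in the headache diary, and report it by arm.
3. Add a sensitivity analysis of the week-12 result that accounts for this use. It should not assume that readings after use are missing at random, because use is likely to be driven by pain. One way is to impute those readings with a range of shifts and report where the conclusion changes.

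**Cost.** One edited paragraph, one diary line and one extra analysis; the sample size does not change. The downside is that participants forgo this class of CM therapy for 8 more weeks, with acetaminophen as the named rescue. Some may deviate or withdraw, and the 15% allowance in 2.9 was set for the present design.

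**Fallback.** If the sponsor will not extend the full ban, bar marketed XFZY alone to week 12 and keep items 2 and 3.

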### 2.6. Drug Compliance

The drug compliance is measured by the tablet count. The patients are asked to return the packaging from the drugs they have already taken at each follow-up visit, throughout the study period. The formula is based on the amount of medication taken divided by the total amount of medication to be taken, and ≥80% will be considered high compliance.

### 2.7. Outcome Measures

#### 2.7.1. Primary Outcome

The primary outcome is the change in mean headache intensity from the baseline to the end of the 12th week. Headache intensity will be measured along a 10 cm visual analogue scale (VAS), with “none” and “very severe” at the extremes of the spectrum.

#### 2.7.2. Secondary Outcomes

The secondary outcomes are the area-under-the-headache curve (AUC), calculated by the sum of the daily headache duration (hours) multiplied by the daily headache intensity for each observed period and, then, divided by the observation period; headache frequency, defined as a ≥50% reduction by number of days with a headache or attacks per evaluation period; headache hours in each observed period; rescue medication use for unbearable pain 2 hours after taking the drugs; QBS pattern measurement by a qualified CM physician; quality of life measured by the EuroQol-5-Dimensions-5-Level (EQ-5D-5L) granted by the EuroQol Group [32, 33]; global evaluation of medication assessed by a simple verbal scale; health economic indexes calculated by the cost of registration, laboratory testing, drugs (other than the experimental drug), hospital admission, transportation, average monthly income, and costs incurred by family caregivers. Participants will be asked to complete a headache diary throughout the trial. The primary outcome and the first four secondary outcomes will be extracted from the headache diary.  Table 2 shows the timing for all outcome measures in the study.

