### 2.2. Participants

We will recruit potential eligible participants via newspaper advertisements, notice boards, and outpatient visits, and also pay attention to whether the recruitment and enrollment progress reached the target sample size. Patients who meet the inclusion criteria and sign informed consent forms will enter the screening period; otherwise, they will be excluded before randomization.

Patients in each center will be diagnosed and differentiated by a senior neurologist and will be observed by a neurologist at a specialist clinic. TTH diagnostic criteria include (1) Western medicine diagnosis based on the criteria of the International Classification of Headache Diseases-3 (ICHD-3) published by the International Headache Society (IHS) in 2018 [5] and (2) pattern diagnosis according to a validated QBS diagnostic scale [29] (Table 1).

Eligibility criteria are as follows: (1) TTH must have occurred for at least 1 year, at least 2 days per month (unlimited frequency), and at least one TTH attack needs to have lasted over 4 hours; (2) a visual analogue scale (VAS) score ≥3 cm; (3) the first onset of TTH need to have happened before the age of 50 years; (4) aged 18–65 years; and (5) CM pattern differentiation is QBS.

Exclusion criteria are (1) concurrent migraine; (2) ailment diagnosed as secondary headache by computed tomography (CT) and transcranial Doppler (TCD) within the previous 6 months; (3) having serious primary diseases such as those of the cardiovascular, liver, kidney or hematopoietic system, and psychosis (schizophrenia, epilepsy, alcoholism, and anorexia) or major neuropsychiatric diseases; (4) labs showing increase in alanine aminotransferase (ALT) or aspartate aminotransferase (AST) over twice the upper limit of the normal range or an increase in creatinine over 1.5 times of the upper limit of the normal range; (5) suffering from other severe pain-inducing diseases, such as cancer; (6) patients with a Self-rating Anxiety Scale (SAS) greater than 59 or Self-rating Depression Scale (SDS) greater than 62; (7) potential allergy to XFZY; (8) women who are either pregnant, lactating, or planning to get pregnant; and (9) participating in other clinical trials within the previous month.

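### Headache frequency is scored only as a ≥50% reduction, although entry runs from 2 headache days a month with no upper limit; a baseline-adjusted headache-day count should be the main frequency measure

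*Protocol article*

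**What the plan says.** The outcome is defined in two places. Section 2.7.2 gives "headache frequency, defined as a ≥50% reduction by number of days with a headache or attacks per evaluation period". The headache-frequency row of Table 2 reads "Defined as a ≥50% reduction by the number of days with a headache or attacks per evaluation period; headache hours for each observed period". Both fix a yes/no response, and neither that row nor any other lists a number of headache days or attacks, or a change in that number, as an outcome.

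The entry criterion in section 2.2 asks for headache on "at least 2 days per month (unlimited frequency"). The Discussion adds: "Both ETTH and CTTH patients are target populations of this study". One relative cut therefore applies to everyone from 2 days a month to near-daily headache.

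Two continuous outcomes come from the same diary. Headache hours are given in Table 2 as "The total hours in each observed period". AUC is "calculated by the sum of the daily headache duration (hours) multiplied by the daily headache intensity for each observed period", then divided by the length of the period.

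**The concern.** A single percentage cut behaves differently across so wide a baseline range. At the entry floor it is one day away from no change, so ordinary month-to-month variation makes responders in both arms and dilutes the contrast. At high baselines it is hard to reach, so a large fall short of half scores zero. Because it is the only frequency measure, the result reported as headache frequency uses less information than the diary holds. At stake are the sensitivity of one secondary outcome and the way its responder percentages are read. The primary VAS outcome and the sample size do not depend on it.

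**Working it through.** The plan gives no expected responder rate, baseline distribution or power for this outcome, so there is no figure of its own to reproduce.

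**Inputs from the article.** Response cut ≥50% (2.7.2, Table 2); entry from 2 days a month, no ceiling (2.2); 87 per group with 15% allowed for loss (2.9), so 87 × 0.85 = 73.95, about 74 evaluable per arm.

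**Assumptions.** Baseline and follow-up windows of 28 days each; days as the counted unit; headache independent from day to day.

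**Step 1, the rule itself.** From 2 to 1: (2 − 1)/2 = 50%, a response. From 20 to 11: (20 − 11)/20 = 45%, 9 days fewer, not a response.

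**Step 2, response with no true change.** Let m be a patient's true mean days per 28, and let baseline B and follow-up F both be binomial(28, m/28). Among patients with at least one baseline day,

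P(response) = Σ over b ≥ 1 of P(B = b) × P(F ≤ b/2), divided by P(B ≥ 1).

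| m (days per 28) | 2 | 3 | 4 | 6 | 8 | 15 |
|---|---|---|---|---|---|---|
| Chance response | 36% | 27% | 20% | 13% | 8% | 0.7% |

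As a hand check, fix the baseline at exactly 2: P(F ≤ 1) = (13/14)^28 + 28 × (1/14) × (13/14)^27 = 0.126 + 0.270 = 0.396. Requiring at least 2 observed baseline days at m = 2 gives 46%.

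**Step 3, the other end.** With the baseline fixed at 20 days and a true 30% reduction, F is binomial(28, 14/28) and P(F ≤ 10) is about 9%. At 25 days it is about 3%.

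**Step 4, power.** Simulated trials with 74 per arm and true means drawn as 2 + gamma(shape 1.2, scale 5), capped at 26 (mean about 8). The responder rates are compared by a two-proportion test, and log(count + 1) by ANCOVA on baseline. The mean reduction is 30% throughout, in two patterns: every treated patient improves by 30%, or 40% of treated patients improve by 75% and the rest not at all (0.40 × 75% = 30%). Extra variation means that a patient's own rate varies between windows with log-SD 0.4.

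| Pattern of effect | Extra variation | Responder test | Log-count ANCOVA |
|---|---|---|---|
| Uniform 30% | none | 82% | 99% |
| Uniform 30% | log-SD 0.4 | 59% | 83% |
| 40% improve by 75% | none | 99% | 99% |
| 40% improve by 75% | log-SD 0.4 | 88% | 95% |

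Levels depend on how the extra variation is coded. Another run of the second row gave 67% against 89%, so the gap of 22 to 24 points is steadier than either level. In the last row, ANCOVA on untransformed counts reached only 76%, below the responder test. With no effect, both the responder test and the log-count ANCOVA rejected in about 5% of trials, and the overall chance response in this population was 12–13% without and 21–23% with the extra variation.

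**The case against.** The strongest case on the other side has four parts.

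- **Reductions are captured elsewhere.** A reader might infer that reductions below half vanish from the trial. They do not: headache hours and AUC are continuous, and a patient going from 20 to 11 days improves on both unless headaches lengthen to offset it. This stands. However, hours mix frequency with duration and AUC adds intensity; neither counts days.
- **The comparison is valid.** A reader might infer bias, or that the responder result says nothing about treatment. The documents do not support that. The trial is randomised, double-blind and placebo-controlled, chance responders arise in both arms, and type I error is about 5%. What the chance rates limit is reading one arm's percentage as the share helped by treatment.
- **The analysis text may already cover it.** Section 2.10 speaks of comparing changes for primary and secondary outcomes, and Table 2 lists frequency at week 0, when no reduction can yet exist, so a count must be recorded. This shows that the data will be there, but it does not make the count an outcome. Nor is this detail left to an unseen analysis plan: the definition is stated, twice.
- **The power loss rests on assumptions.** This stands. The article gives no baseline distribution, baseline window or expected reduction. A uniform effect is unfavourable to a responder cut; if a minority responds strongly, the gap nearly closes, and against raw counts it can reverse. A claim that the cut always loses substantial power would go too far.

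**Conclusion.** The point holds as a cheap improvement to a secondary outcome. One relative cut, as the only frequency measure over an unlimited baseline range, counts one-day changes at the entry floor and ignores nine-day changes higher up. The direct arithmetic needs no assumption. The chance-response rates (36%, 20% and 8% at 2, 4 and 8 days) rest on independent days and equal 28-day windows, and the highest applies only to patients at the floor. The power cost is about 17 to 24 points under a uniform 30% reduction (82% against 99%; 59% against 83%) and 0 to 7 points if a minority responds strongly (99% against 99%; 88% against 95%). In these scenarios the log-count analysis did at least as well as the cut, which is why the scale of analysis matters. The primary conclusion and the validity of the randomised comparison are unaffected.

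**What to change.** In section 2.7.2 and the headache-frequency row of Table 2, add the number of headache days per 28 days, weeks 9–12 against baseline, as the main frequency measure. Compare arms with baseline headache days as covariate on a log or ratio scale: a negative binomial model, or ANCOVA or a mixed model on log counts. Avoid untransformed counts, given the result above.

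Keep the ≥50% responder rate as supportive, interpret it only as a between-arm difference, and show it separately for low and higher baseline counts.

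Do not add a rule that the reduction must be confirmed in two consecutive 28-day blocks. In simulation it lowers chance response (from 36% to 16% at 2 days) but also lowers power (from 67% to 63% in the uniform-effect run with extra variation), so it does not cure the loss.

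The cost is a change of wording and one more model on diary data already collected, with no extra patients or visits. The downside is a headline in headache days, as a difference or ratio, in place of a responder percentage.
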